### Covid-19 contingency plan

Due to the COVID-19 pandemic in 2020, we developed an alternative protocol in the event we are not able to assess children face-to-face. See Supplementary Table 1 for details. At the time of submission in May 2021, the Covid-19 contingency plan was not activated.

### Follow up correspondence with participants

Follow-up correspondence with a summary report of the child’s assessments will be sent to the mother within six weeks of the completion of the Ages and Stages Questionnaires (younger cohort) or the on-site assessments (older cohort). An offer to discuss the results with the study coordinator with contact details will be provided. If the woman wishes the PALM study to share the results of the assessments with her child’s health care provider, written consent will be obtained for this information sharing.

For the participants in the CNV reanalysis group, an additional letter will be sent to them with the results of the updated analysis. Participants will be offered a clinical referral to discuss the findings if the CNV classification has changed from the original prenatal report.

### Statistical methods of analysis and power calculations

#### Objective 1:

The primary outcome for the 2–7-year-old group is the WPPSI-IV full IQ score. The WPPSI-IV is standardized to be normally distributed with a mean of 100 and standard deviation of 15 in the general population (variance of 30). It is therefore possible to perform the primary analysis as a single group comparison by t-test of the WPPSI-IV full IQ score in the children enrolled in this study with the population norm. A between-group analysis of the WPPSI-IV for the CNV study group and control (non-CNV) group cohorts will be done. The results from the children with VUS will be analyzed separately from those with pathogenic CNVs (pCNVs).

If 300 participants with VUS are enrolled, this will yield > 95% power and 95% confidence to detect a 3-point difference (0.2SD) in mean IQ from the norm assuming that the standard deviation is 15.

Our study cohort of women with VUS are a heterogenous group with varying indications for testing. As the presence of a fetal structural abnormality is likely to be a modifier of all assessed outcomes, a stratified analysis of the CNV cohort with and without this indication for prenatal diagnosis will be performed. An audit of the VPDD data shows that those with a fetal structural abnormality comprise two thirds of the VUS study cohort, leaving 100 to study without such an abnormality. The required sample size is therefore a minimum of 87 women without a fetal structural abnormality in each of the study and control cohorts to detect a 3-point difference in mean IQ (95% power, 95% confidence).

For the group with pCNVs, a larger difference in mean IQ is expected between those with pCNVs and those without any CNV. A minimum of 13 participants in the pCNVs cohort is required to detect a mean difference of 8 IQ points with 95% power and 95% confidence. It is expected that this analysis can be performed on the subgroup with the most common pCNV (22q11.2 deletion syndrome), which is detected prenatally in approximately 7 cases per year. If 100% progressed to live outcome, there would be at least 35 children in the cohort (born from 2013-2018) that would be able to perform the WPPSI-IV. Less than 50% would be required to be available for recruitment to meet the minimum sample size of 13.

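### The minimum sizes of 87 per group and 13 pCNVs come from an IQ variance of 30 instead of 225, so the 95% power stated for them does not hold

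*Protocol article*

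**What the plan says.** All the relevant statements are in the protocol article, Statistical methods of analysis and power calculations, Objective 1.

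- The IQ scale is given a "standard deviation of 15 in the general population (variance of 30").
- For 300 VUS tested against the population norm, the aim is to "detect a 3-point difference (0.2SD) in mean IQ from the norm assuming that the standard deviation is 15".
- For VUS without a structural abnormality, of whom 100 are expected, the plan requires "a minimum of 87 women without a fetal structural abnormality in each of the study and control cohorts", in order "to detect a 3-point difference in mean IQ (95% power, 95% confidence").
- For pathogenic CNVs, "a larger difference in mean IQ is expected between those with pCNVs and those without any CNV", and the size follows: "A minimum of 13 participants in the pCNVs cohort is required to detect a mean difference of 8 IQ points with 95% power". No control number is attached to the 13.
- The 13 is then used to present a 22q11.2 deletion analysis as feasible, because fewer than half of 35 potential children would have to be recruited.

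The Sample size section plans 267 VUS, 87 pCNVs and 358 controls. Table 2 gives the WPPSI-IV only to the older cohort (2 years 7 months and above at enrolment); children of 12 to 30 months receive the ASQ instruments.

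**The concern.** A variance is the square of the SD, so SD 15 and variance 30 cannot both be right. The question is whether the 30 is a harmless slip in a parenthesis or whether it entered the calculations. If it entered them, the section uses two different spreads for the same score: 15 for the one-sample VUS calculation and about 5.5 (√30) for the two-group sizes.

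Two design statements depend on the answer. The 87 presents the stratum of about 100 VUS children without structural abnormality as large enough for 3 points. That stratum matters because controls with structural abnormalities are excluded (Study population), so it is the like-for-like comparison with them. The 13 supports the claim that the 22q11.2 subgroup can be analysed alone. If both sizes are far too small, a non-significant difference in either analysis says much less than the stated 95% power implies.

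**Working it through.** **Inputs from the article.** SD 15; stated variance 30; differences of 3 and 8 points; 95% power; 95% confidence, taken as two-sided 5%; 100 VUS without structural abnormality; 35 potential 22q11.2 children; 87 pCNVs; 358 controls. Allocation is 1:1 for the 87, as stated; for the 13 it is an assumption.

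**Step 1: reproduce the plan's figures.** Size per group = 2 × (1.960 + 1.645)² × variance / difference², with (1.960 + 1.645)² = 12.995.

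| Variance | 3 points | 8 points |
|---|---|---|
| 30 | 2 × 12.995 × 30 / 9 = 86.6, so 87 | 2 × 12.995 × 30 / 64 = 12.2, so 13 |
| 225 | 2 × 12.995 × 225 / 9 = 649.7, so 650 | 2 × 12.995 × 225 / 64 = 91.4, so 92 |

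Variance 30 returns both stated sizes. With SD 15, one-sample or two-sample, one-sided or two-sided, at 80%, 90% or 95% power, nothing falls below 155 for 3 points or 22 for 8 points.

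**Step 2: power at SD 15.** Standard error = 15 × √(1/n₁ + 1/n₂). Power is approximately Φ(difference / standard error − 1.960); the last column uses the noncentral t.

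| Comparison | Difference | Difference / SE | Power |
|---|---|---|---|
| 87 v 87 | 3 | 3 / 2.274 = 1.319 | 26% |
| 100 v 100 | 3 | 3 / 2.121 = 1.414 | 29% |
| 100 v 358 | 3 | 3 / 1.697 = 1.768 | 42% |
| 13 v 13 (assumed) | 8 | 8 / 5.883 = 1.360 | 26% |
| 13 v 358 | 8 | 8 / 4.235 = 1.889 | 47% |
| 35 v 358 | 8 | 8 / 2.657 = 3.012 | 85% |
| 87 v 358 | 8 | 8 / 1.793 = 4.462 | over 99% |

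The 35 v 358 row is the best case for 22q11.2: every potential child live-born, recruited and tested. Read as one-sample tests against the norm, 87 gives 45% for 3 points and 13 gives 42% for 8 points.

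**Step 3: what the planned cohort can detect.** Detectable difference = 15 × √(1/n₁ + 1/n₂) × (1.960 + z), with z = 0.842 for 80% and 1.645 for 95% power. The VUS number is 100 (one third of 300) or 89 (267 / 3). The documents do not give the proportion with a WPPSI-IV score, so 5/7 to 6/7 of each group is an assumed range.

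| Tested | VUS v controls | 80% power | 95% power |
|---|---|---|---|
| All | 100 to 89 v 358 | 4.8 to 5.0 | 6.1 to 6.4 |
| 6/7 | 86 to 76 v 307 | 5.1 to 5.4 | 6.6 to 6.9 |
| 5/7 | 71 to 64 v 256 | 5.6 to 5.9 | 7.2 to 7.6 |

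**Step 4: pCNVs needed for 8 points at 95% power.** 1/n₁ = (8 / (15 × 3.605))² − 1/n₂ = 0.02189 − 1/n₂.

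| Tested | Controls | pCNVs needed | pCNVs available |
|---|---|---|---|
| All | 358 | 52.4, so 53 | 87 |
| 6/7 | 307 | 53.7, so 54 | about 75 |
| 5/7 | 256 | 55.6, so 56 | about 62 |
| 4/7 | 205 | 58.8, so 59 | about 50 |

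**The case against.** The arithmetic error cannot be defended, but its reach can be overstated, and four limits stand.

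First, a reader might infer that the study's two-group IQ comparisons in general have about 26% power. The documents do not support that. The 26% belongs to the stated minimums at 1:1, which the article fixes only for the 87. The planned control group is 358, and the pooled pCNV comparison would exceed 99% power for 8 points if all 87 were tested.

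Second, a reader might infer that the primary analysis or the recruitment targets collapse. They do not rest on the error. The article allows the primary analysis to be a one-sample test against the norm, and the calculation for 300 VUS uses SD 15. (Its power is about 93% two-sided and 97% one-sided; that is separate from the variance.) The targets of 354 and 358 come from expected participation rates.

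Third, corrected figures that count every recruit would be too favourable, because only the older cohort has the WPPSI-IV.

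Fourth, the article states no rule that a null result is to be read as reassurance, so that harm is possible rather than planned.

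The provision under Poor recruitment to pool with the United States cohort does not answer the point: it is tied to missed recruitment targets, and these sizes fail even if targets are met.

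**Conclusion.** Wrong as written. The stated variance contradicts the stated SD, and both minimum sizes come from the wrong value. At SD 15 they are too small by a factor of 225 / 30 = 7.5, and no standard reading brings either near 95% power.

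What fails is specific: the 87 per group for 3 points, the 13 for 8 points, and the 22q11.2 feasibility statement, which misses 95% even with all 35 children and all 358 controls. The 3-point comparison for VUS without structural abnormality is not adequately powered at the expected numbers, with or without the full control group. Whether the pooled pCNV comparison reaches 95% power for 8 points depends on how many of the 87 are old enough for the test.

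This rests on SD 15 in both groups, a two-sided 5% test, no covariate adjustment, and, for the 26% at 13 pCNVs, an assumed equal number of controls.

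**What to change.** Change wording only, with no change to enrolment:

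1. Correct the variance to 225.
2. Withdraw 87 and 13 as minimums for 95% power, together with the 22q11.2 feasibility statement.
3. State the number of children in each group expected to have a WPPSI-IV score and the number of controls used, and give detectable differences on that basis. If all are tested, 89 to 100 VUS against 358 controls detect about 4.8 to 5.0 points at 80% power and 6.1 to 6.4 at 95%. If 5/7 to 6/7 are tested, the ranges are about 5.1 to 5.9 and 6.6 to 7.6.
4. For pCNVs, state that about 53 to 56 tested children are needed for 8 points at 95% power across that range, and that the planned 87 meet this only if enough are old enough to be tested.
5. State that the stratum of VUS without structural abnormality is not adequately powered for a 3-point difference.

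The cost is a few sentences and a less favourable statement of power. No procedure, visit or recruitment target changes.

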## Methods/Design

### Aims

The PALM cohort study will establish and follow-up a cohort of mother-child pairs who had a prenatal diagnosis of a CNV from 2013-2019 (inclusive) in the Australian state of Victoria. Victoria has approximately 78,000 births per year and a median maternal age of 31.5 years [13]. Approximately 2-3% of all pregnant women undergo prenatal diagnosis per year [14].

The study aims are to:
Compare the developmental, social-emotional and health status of children with a prenatal diagnosis of a prenatal CNV with those children with no CNV detected on CMA.Measure the impact of a prenatal diagnosis of a CNV on maternal perceptions of child health, behavior, and development.Determine the proportion of CNV ascertained prenatally that are reclassified from unknown or uncertain to benign or pathogenic after two or more years using contemporaneous curation resources.

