### Study population

Each year the VPDD receives prenatal diagnostic testing results on approximately 150 pregnancies with CNVs, and 1000 pregnancies with no CNVs. We will recruit an equal number of participants with and without CNVs, frequency matched for fetal sex, trimester at prenatal diagnosis, maternal age group (by decade) and calendar year of testing. Due to the modifier of structural anomaly on childhood outcomes, women with fetal structural abnormalities will be excluded from the control group of pregnancies with no CNVs.

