### Sample size

The VPDD from 2013-2019 has recorded an average of 147 CNVs (85 VUS, 62 pCNVs) each year. Our total potential CNV cohort for the proposed 7-year study period will be approximately 1029.

We expect losses of potential recruits due to failed contact tracing, language ineligibility, perinatal loss, and refusal of consent, and therefore conservatively estimate a final sample size of 354 women for the CNV cohort. This is based on 45% recruitment of women with fetal VUS (n=267), and 20% recruitment rate for pathogenic CNVs (n=87). This is in line with participation rates in the NICHD microarray cohort where they achieved 41%, 56% and 70% participation rates for those with pathogenic, VUS or benign/normal CMA results respectively [16]. There are 7155 potential eligible controls in the study period. We will require 5% of women with normal CMA results to be recruited to form the control cohort (n=358).

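### The WPPSI-IV analysis given primary status compares enrolled children with the population norm, while Aim 1 asks for CNV versus no CNV; the planned control comparison should be primary, in the stratum without structural anomaly, with its power restated

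*Protocol article*

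**What the plan says.** **Question.** The Aims section sets out to compare children "with a prenatal diagnosis of a prenatal CNV with those children with no CNV detected on CMA". The Study population section provides the comparator: "We will recruit an equal number of participants with and without CNVs, frequency matched for fetal sex", and also on trimester, maternal age group and year of testing. The Sample size section expects 267 VUS, 87 pathogenic CNVs and 358 controls.

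**Analysis.** Under Objective 1 the article describes the IQ score's norm (mean 100, SD 15) and continues: "It is therefore possible to perform the primary analysis as a single group comparison by t-test of the WPPSI-IV full IQ score", with the norm as reference. The next sentence reads "A between-group analysis of the WPPSI-IV for the CNV study group and control (non-CNV) group cohorts will be done", without saying that this comparison is primary. VUS and pathogenic CNVs are to be analysed separately. Adjustment for maternal age, parental education and gestational age at birth is described under Secondary outcomes.

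**Sizing.** Objective 1 contains three sizing statements:
- 300 VUS against the norm, for 3 points with more than 95% power;
- 87 per group without structural anomaly, VUS versus control, for 3 points with 95% power;
- 13 pathogenic CNVs, for 8 points against children without a CNV, with 95% power.

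**Structural anomaly.** In the Study population section, "women with fetal structural abnormalities will be excluded from the control group of pregnancies with no CNVs". Objective 1 says that two thirds of the VUS group have such an anomaly, expects it to modify every outcome, and plans a stratified analysis.

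**The concern.** The test with primary status does not estimate the contrast in Aim 1. It asks whether the enrolled children average 100. That answers the CNV question only if the same families' children would have averaged 100 without a CNV.

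Nothing in the article supports this. The families come from the 2–3% of pregnant women who have prenatal diagnosis. They must consent in English, live in Victoria and be able to bring the child to assessments, and they respond to a mailed invitation. The article itself lists parental education and maternal age among modifiers and confounders, and a one-sample t-test adjusts for neither.

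The target difference is only 3 points, so a modest offset matters. An upward offset could hide a real VUS deficit, and a downward one could create a false deficit. The Discussion intends the VUS results to inform what is disclosed in pregnancy and whether structured follow-up is needed. The BITSEA, the primary outcome of Objective 2, is by contrast compared with controls.

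**Working it through.** **Inputs.** From Objective 1: SD 15, differences of 3 and 8 points, n = 300, 87 and 13, and two thirds of VUS with anomaly. From Sample size: 267 VUS, 87 pathogenic CNVs, 358 controls. Assumed: two-sided alpha 0.05 (the article says 95% confidence and gives no sidedness), normal approximation, no covariate adjustment.

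**1. The plan's own figure.** One-sample power = Φ(δ√n/SD − 1.96). For n = 300 and δ = 3: 3√300/15 = 3.464, so power = Φ(1.504) = 93.4%. One-sided, Φ(3.464 − 1.645) = 96.6%, which meets the stated figure. At the expected 267: 3√267/15 = 3.268, giving 90%.

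**2. Effect of an offset b from 100** (assumed; the documents give none). With no CNV effect and n = 267, P(reject) = Φ(b√267/15 − 1.96) + Φ(−b√267/15 − 1.96), where √267/15 = 1.089.

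| b (points) | Rejection with no CNV effect | Power for a true deficit of 3 when the offset is +b |
|---|---|---|
| 0 | 5% | 90% |
| 1 | 19% | 59% |
| 2 | 59% | 19% |
| 3 | 90% | 5% |
| 4 | 99% | net difference +1: wrong sign |

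The last column uses the same formula with the net difference b − 3. Noncentral t results differ by less than half a point.

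**3. Two-group power.** SE = 15√(1/n₁ + 1/n₂), power = Φ(δ/SE − 1.96), and the detectable difference at 80% power = (1.96 + 0.842) × SE. VUS without anomaly: one third of 267 = 89, or the article's own 100 (one third of 300).

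| Contrast | SE | Power, 3 points | Detectable at 80% |
|---|---|---|---|
| All VUS, 267 v 358 | 1.213 | 70% (69.6%) | 3.4 |
| VUS without anomaly, 100 v 358 | 1.697 | 42% | 4.8 |
| VUS without anomaly, 89 v 358 | 1.777 | 39% | 5.0 |

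For pathogenic CNVs and 8 points, 87 v 358 gives 99% and 13 v 358 gives 47%. The numbers are upper limits, because only the older cohort takes the WPPSI-IV.

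**4. The stated between-group sizes.** n per group = 2 × variance × (1.96 + 1.645)²/δ², with (1.96 + 1.645)² ≈ 13.0. The article describes the norm as having SD 15 and a variance of 30, but 15² = 225.
- Variance 30: 3 points gives 86.6, so 87; 8 points gives 12.2, so 13. Both stated figures reproduce.
- Variance 225: 3 points gives 650; 8 points gives 92.
- At SD 15, 87 v 87 has SE = 15√(2/87) = 2.274 and power Φ(1.319 − 1.96) = 26%; 13 v 13 has 27% for 8 points.

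The between-group sizes therefore cannot be carried over unchanged if that comparison becomes primary.

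**The case against.** **The wording is permissive and controls are used.** This stands. The article says that a one-sample primary analysis is possible, commits in the next sentence to a between-group analysis, and frames two of its three sizing statements between groups. The one-sample test refers to the children enrolled, which may include controls. A reader might infer that the control cohort is discarded; the documents do not support that. What remains is that primary status and the whole-group VUS power go to the comparison that does not match the aim. An analysis plan may settle the order, but the article's statement conflicts with its own aim.

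**No bias is shown.** This also stands. No passage gives an offset, so the rejection rates illustrate sensitivity and do not predict anything. A reader might also take 20% and 45% as volunteer rates among invited families. They are yields from all recorded CNVs (85 × 7 × 0.45 ≈ 268; 62 × 7 × 0.20 ≈ 87) and already absorb failed tracing, language ineligibility, perinatal loss and refusal.

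**Controls need not cure the problem.** Partly right. Only the offset common to both groups cancels, and families given an uncertain result may take part for different reasons. In addition, comparing all VUS with controls would credit the effect of structural anomaly to the VUS. This determines which between-group contrast should be primary. It does not favour the norm, which shares the anomaly problem and adds the shared selection.

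**Conclusion.** The point holds as a mismatch between the aim and the analysis given primary status. The norm comparison carries any offset of enrolled families in full, and with 267 VUS even 1 to 2 points would raise a nominal 5% rejection rate to 19–59%. This rests on an assumed offset, SD 15 and a two-sided 5% test. It does not show that the IQ result will be biased, nor that controls go unused.

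It would also be too strong to infer that relabelling the comparison of all VUS with controls is enough. Anomaly is excluded on one side and present in two thirds of the other, so the cleaner contrast is the anomaly-free stratum. Power there is at most about 39–42% for 3 points, against the more than 95% stated for the norm test and the 95% stated for 87 per group.

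**What to change.** 1. Name the between-group comparison as the primary WPPSI-IV analysis.
2. For VUS, base it on the stratum without fetal structural anomaly that Objective 1 already plans, adjusted for the confounders listed under Secondary outcomes. Report the all-VUS contrast alongside, and state that its difference cannot be attributed to the VUS alone.
3. Report pathogenic CNV versus control with the same stratification.
4. Report the comparison with the norm descriptively for CNV children and controls alike, so that any offset of the enrolled families is visible.
5. Correct the variance and restate the between-group sizes and power at SD 15: about 39–42% for 89–100 v 358 (detectable difference 4.8–5.0 points at 80% power) and about 70% for 267 v 358 (3.4 points). Reduce these for the share of children old enough for the WPPSI-IV.

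**Cost.** No new data or enrolment, but the sample-size text must be rewritten and the stated power becomes clearly less favourable. The primary VUS result would rest on about one third of the VUS children, and those with an anomaly have no like-for-like controls. Adjustment may recover some precision; the documents give nothing to size that.

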Quantitative survey	‘Younger cohort’ children who are 12-30 months old at the time of enrolment	Ages and Stages Questionnaire-3	Parent	Online or hard copy. 20-30 minutes.
		Ages and Stages Questionnaire Social Emotional-2	Parent	
Quantitative survey	‘Older cohort’ children who are 2 years 7 months to 7 years 7 months at the time of enrolment	The Vineland-II Adaptive Behavior Scale (VABS)	Parent	Online or hard copy. 20-60 minutes
Psychologist assessment		Wechsler Preschool and Primary Scale of Intelligence IV (WPPSI-IV)	Psychologist	In person. 20-60 minutes
Clinical assessment		Clinical assessment by study pediatrician: measurements of height, weight, and head circumference; history and physical examination	Paediatrician	In person. 20-60 minutes
**Outcome 3:** The frequency of copy number variants that have a change in classification after reanalysis after ≥2 years will be presented in a descriptive analysis. For the participants in the reanalysis group, an additional letter will be sent to them with the results of the updated analysis.				
Clinical standard laboratory software and databases in use during 2021-2022	Children who were prenatally diagnosed with a copy number variant of uncertain or unknown significance	Affymetrix Chromosome Analysis Suite (ChAS) software	Cytogenetics Laboratory	n/a
		DatabasE of Chromosomal Imbalance and Phenotype in Humans using Emsembl Resources (DECIPHER)	Cytogenetics Laboratory	
		International Standards for Cytogenomic Arrays (ISCA) database	Cytogenetics Laboratory	
		Online Mendelian Inheritance in Man (OMIM)	Cytogenetics Laboratory	

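### The claim of more than 95% power for the VUS comparison counts 300 children with an IQ score, but the plan expects 267 VUS recruits of all ages, and only part of them will take the WPPSI-IV

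*Protocol article*

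**What the plan says.** The section on statistical methods and power, under Objective 1, proposes to "perform the primary analysis as a single group comparison by t-test of the WPPSI-IV full IQ score" against the population norm. The power statement for that test reads "If 300 participants with VUS are enrolled, this will yield > 95% power and 95% confidence to detect a 3-point difference (0.2SD", and continues "in mean IQ from the norm assuming that the standard deviation is 15". Whether the test is one- or two-sided is not stated. The same section puts fetal structural abnormality at two thirds of the VUS cohort, "leaving 100 to study without such an abnormality".

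The Sample size section gives the expected yield. It starts from "an average of 147 CNVs (85 VUS, 62 pCNVs) each year" over seven years and continues: "This is based on 45% recruitment of women with fetal VUS (n=267), and 20% recruitment rate for pathogenic CNVs (n=87".

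Table 2, under Data collection, assigns the WPPSI-IV to the older cohort, "children who are 2 years 7 months to 7 years 7 months at the time of enrolment". Children aged 12 to 30 months at enrolment receive the Ages and Stages Questionnaires instead, and for the youngest group those scores are the primary outcome.

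**The concern.** The power statement for the primary IQ comparison uses a number of VUS children larger than the article's own recruitment estimate. It also treats every VUS recruit as having an IQ score, although the younger cohort will not take the test. The article makes an age reduction for 22q11.2 deletion, where it counts only children able to do the WPPSI-IV, but makes none for VUS.

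The consequence lies in how a null result would be read. The claim implies less than a 5% chance of missing a true 3-point deficit. On the plan's own recruitment (two-sided) that chance is about 10%, and higher once age is allowed for. The Discussion intends the VUS results to inform whether such findings are usefully disclosed in pregnancy, so an overstated power figure would lend a null result more reassurance than it has earned.

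**Working it through.** **Inputs.** Difference 3 points, SD 15, one-sample t-test, 95% confidence (Objective 1). VUS per year 85, seven years, 45% recruited (Sample size). WPPSI-IV age window five years wide (Table 2). Testing from January 2013 to December 2019, seven years (Study design).

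**Formula.** Power = Φ(3√n / 15 − z), with z = 1.960 for two-sided 5% and 1.645 for one-sided 5%. Each result was checked with the exact noncentral t.

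**Step 1: the article's own figure, n = 300.** 0.2 × √300 = 3.464.
- Two-sided: Φ(1.504) = 93.4% (exact t 93.2%).
- One-sided: Φ(1.819) = 96.6% (exact t 96.5%).

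The printed figure therefore reproduces one-sided and falls just short two-sided.

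**Step 2: expected VUS recruits.** 85 × 7 = 595, and 0.45 × 595 = 267.75, which the article gives as 267.

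**Step 3: share in the WPPSI-IV age window.** The article does not state it. Two values can be drawn from the text:
- A five-year age window over seven years of testing gives 5/7. The 22q11.2 count agrees: 35 children at 7 per year is five years' worth.
- The same sentence labels those children as born from 2013 to 2018, which is six years and suggests 6/7.

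So 267 × 5/7 = 191 and 267 × 6/7 = 229.

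**Step 4: power at these numbers (exact t in brackets).**

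| VUS children with an IQ score | Two-sided 5% | One-sided 5% |
|---|---|---|
| 300 (as claimed) | 93.4% (93.2%) | 96.6% (96.5%) |
| 267 (all recruits) | 90.5% (90.3%) | 94.8% (94.7%) |
| 229 (6/7) | 85.7% (85.4%) | 91.6% (91.5%) |
| 191 (5/7) | 78.9% (78.5%) | 86.8% (86.6%) |

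The number needed for 95% power is (15 × (z + 1.645) / 3)²: 325 two-sided, 271 one-sided. Both exceed 267.

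**Step 5: VUS without a structural abnormality.** The article's 100 is 300 / 3. From the planned number it is 267 / 3 = 89. With an IQ score: 89 × 5/7 = 64 and 89 × 6/7 = 76.

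**Step 6: the article's minimum of 87.** The two-sample formula is n per group = 2 × variance × (1.960 + 1.645)² / difference².
- Variance 30: 2 × 30 × 12.995 / 9 = 86.6, so 87. For 8 points, 2 × 30 × 12.995 / 64 = 12.2, so 13.
- Variance 15² = 225: 2 × 225 × 12.995 / 9 = 649.7, so 650. For 8 points, 91.4, so 92.

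Both minimums thus come from the printed "standard deviation of 15 in the general population (variance of 30", which does not agree with an SD of 15. They are no yardstick for the 89 or the 64 to 76.

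**The case against.** **Sidedness.** A reader might infer that the figure for 300 is itself wrong, because a two-sided test gives 93%. The article does not support that as a firm statement: no sidedness is given, and a one-sided test gives 96.5%. The neighbouring 87 and 13 reproduce only with two-sided 5% (one-sided gives 73 and 11), which makes two-sided the likelier intention. They belong to a different, two-sample test, however, and rest on a wrong variance. This objection stands for n = 300. It does not rescue the claim at 267, where even one-sided power is below 95%.

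**The age share.** A reader might also take 79% as the power of the study. That is only the lower end. It needs 5/7 of recruits in the window, which depends on an enrolment calendar the article does not give. Staggered enrolment could raise the share, and the 2013 to 2018 label points to 6/7. This objection stands, so a range is reported.

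**The recruitment estimate.** The 300 is worded conditionally, and 267 is called conservative. The US microarray cohort, cited in the Sample size section, had 56% participation for VUS. Applied here, 0.56 × 595 = 333, which gives about 95% two-sided if every child took the test, but about 87% at 5/7 (238 children). So better recruitment could recover the claim only if almost no recruits are lost to age. The article also plans to pool with the US cohort if recruitment falls short. That is a contingency and does not support the power quoted for this cohort.

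**The subgroup.** It is tempting to say that VUS children without a structural abnormality fall below the article's required 87. As shown above, 87 is not a valid requirement. Nor does the article rank this subgroup above the others; it calls structural abnormality a likely modifier and plans to stratify by it.

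**Conclusion.** The concern holds in a limited form. The article's planned VUS recruitment does not deliver more than 95% power under either sidedness. At SD 15 and a 3-point difference, power is about 90% two-sided (just under 95% one-sided) if all 267 have an IQ score, and about 79% to 85% two-sided if 5/7 to 6/7 do. The first figure rests only on numbers in the article. The second rests on an assumed age share and on the Table 2 window. The number without a structural abnormality is 89 on the planned recruitment, not 100, with about 64 to 76 having an IQ score under the same assumption.

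The comparison with the norm remains reasonably powered over most of this range. What fails is the stated figure. The variance of 30 behind 87 and 13 is a separate and larger error.

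**What to change.** In Objective 1 and the Sample size section:
- Use one VUS number throughout, reconciling 300 with 267 and 100 with 89, or justify a recruitment rate that yields 300.
- State how many VUS recruits are expected in the WPPSI-IV age window and the enrolment dates assumed. Use one age range: the Abstract, Objective 1 and Table 2 describe it differently.
- State the sidedness of the test.
- Restate power as roughly 79% to 90% (two-sided), with the age-share assumption shown.
- Recalculate 87 and 13 with variance 225 before citing either as a minimum.

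The cost is wording and a short recalculation. Eligibility, assessments and recruitment procedures are unchanged. The price is a less favourable power statement, and a null VUS result would have to be read with that in mind, preferably through its confidence interval.
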